### Sample size

We hypothesize that SLI maneuver might decrease the need for MV during the first 72 hours of life from 35% to 20%. We calculated that 138 newborns must be enrolled in each group to detect this difference as statistically significant with 80% power at a level of 0.05.

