### Randomization

Infants at each unit will be assigned to a block (1st block: gestational age from 25^+0^ to 26^+6^ weeks; 2nd block: gestational age from 27^+0^ to 28^+6^ weeks) and randomly assigned to a treatment group in 1:1 ratio using automatically generated sealed opaque envelopes, which will be prepared at Careggi University Hospital, Florence, Italy, and then distributed to participating centers. Block size will be concealed to investigators to ensure treatment balance between the two arms of the study.

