### Statistical analysis

The primary efficacy analysis will be conducted on an intention-to-treat basis. Clinical characteristics of infants in the SLI and control groups will be described using mean values and SD, median value and range, or rate and percentage. Univariate statistical analysis will be performed using the Student’st-test for parametric continuous variables, the Wilcoxon rank-sum test for non-parametric continuous variables and the chi-square test for categorical variables. A *P*<0.05 will be considered statistically significant. SLI treatment and clinical characteristics which are most likely associated with the need for MV (gestational age, birth weight, antenatal steroids, CRIB score, INSURE procedure and hospital of birth) will be included in multiple logistic regression analysis to assess their independent role in predicting SLI success or failure. Effect estimates will be expressed as relative risk (RR) with profile likelihood-based 95% confidence limits.

An interim analysis is planned when 100 infants are enrolled (50 in each arm).

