### Data processing and monitoring

All study data will be:

1. Screened for out-of-range data, with cross-checks for conflicting data within and between data collection forms by a data manager.

2. Referred back to the relevant center for clarification in the event of missing items or uncertainty.

3. Reviewed by the Chief Investigators (CD, GL) and trial statistician, and they will review the results generated for logic,patterns andproblems Outlier data will be investigated.

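### The interim analysis at 100 infants has no stated purpose or alpha allocation; if it tests efficacy at the only stated threshold, P<0.05, overall type I error rises to about 8.7-8.9%

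*Protocol article*

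**What the plan says.** Three statements in the protocol article bear on this point.

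- **Interim (Statistical analysis).** "An interim analysis is planned when 100 infants are enrolled (50 in each arm"). This is the only mention of an interim. Purpose, endpoint, stopping rule and threshold are not given.
- **Significance rule (Statistical analysis).** After the list of univariate tests, a P value below 0.05 "will be considered statistically significant". No other threshold appears, and this one is not limited to the final analysis.
- **Sample size.** The hypothesis is that SLI "might decrease the need for MV during the first 72 hours of life from 35% to 20" per cent. The enrolment target follows: "We calculated that 138 newborns must be enrolled in each group". Power and significance level are those of one comparison, 80% and 0.05, with no mention of a second look.

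The interim sentence closes the section that begins with the primary efficacy analysis. The Safety section mentions no interim.

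**The concern.** The article fixes the timing and arm sizes of an early look, one unqualified significance threshold, and a sample size for a single test. These fit together only if the interim cannot lead to an efficacy claim, or if a boundary is set somewhere that the article does not mention. A reader who simply follows the article would apply P<0.05 at 100 infants and again at the end, and the stated 0.05 level would then not hold.

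Two things would be at stake. The first is the false-positive rate. The second is the estimate: a claim made at 100 infants would rest on 36% of the planned sample, and results that happen to cross P<0.05 that early overstate the effect on average.

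**Working it through.** **Inputs from the protocol article**
- Event rates 35% (control) and 20% (SLI), power 80%, level 0.05, 138 per arm: Sample size.
- Equal allocation: Randomization ("randomly assigned to a treatment group in 1:1 ratio").
- Interim at 50 per arm, chi-square test for categorical variables, P<0.05: Statistical analysis.
- Final total 2 × 138 = 276, as in the Abstract. The Duration of study section gives 272, so both are tried.
- Sidedness is not stated. It is inferred in step 1.

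**1. Reproduce the planned size.** Two-sided, pooled variance, no continuity correction, mean rate 0.275:

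n = [1.96 × √(2 × 0.275 × 0.725) + 0.842 × √(0.35 × 0.65 + 0.20 × 0.80)]² / 0.15²
= [1.96 × 0.6315 + 0.842 × 0.6225]² / 0.0225 = 137.9, rounded up to **138 per arm**.

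The stated figure is reproduced, with power 80.0% at 138. A one-sided test would need 109 and a continuity-corrected one 151. The plan's figure is therefore that of a single two-sided, uncorrected test with nothing set aside for an interim look.

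**2. Type I error if P<0.05 is applied at both looks.** The information fraction is t = 100/276 = 0.362, and the two test statistics have correlation √0.362 = 0.602. With both critical values at 1.96:

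overall error = 1 − P(|Z1| < 1.96 and |Z2| < 1.96) = **8.75%**.

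With 272 infants, t = 0.368 and the result is 8.73%, so the 276/272 discrepancy has no bearing here.

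**3. Check on the binary outcome.** Chi-square test simulated at 50 and then 138 per arm, 1,000,000 trials at each common event rate:

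| Common rate | Uncorrected | Continuity-corrected |
|---|---|---|
| 20% | 8.9% | 5.6% |
| 27.5% | 8.8% | 6.0% |
| 35% | 8.8% | 6.1% |

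**4. Other readings of the interim.**
- No efficacy claim possible at the interim: 5%.
- Interim threshold P<0.001, final P<0.05: 5.04%.

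**5. If the assumed effect is true (35% versus 20%).** With 50 per arm and the uncorrected test, the chance of P<0.05 at the interim is 39%. In the trials that cross, the mean observed difference is about 23.5 percentage points against a true 15. With the continuity correction the chance is about 32%.

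**6. A boundary that would protect 0.05.** Lan-DeMets O'Brien-Fleming-type spending of two-sided 0.05 at t = 0.362:

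alpha spent at the interim = 2 × [1 − Φ(1.96/0.602)] = 2 × [1 − Φ(3.256)] = 0.0011.

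The final critical value that brings the total to 0.05 is 1.964, or P<0.0495. Simulated power with 138 per arm is about 80% both with this boundary and for the single-look design.

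**The case against.** The strongest counter-argument is that the document never calls the interim an efficacy look. It does not say that P<0.05 applies there, and it does not permit early stopping. The Duration of study section has recruitment running to the full number and the trial ending when the last infant is discharged or dies. Read literally, that is a trial that cannot stop at 100 infants, and an interim that supports no claim leaves alpha at 5%. Boundaries and alpha spending are also details that a journal article commonly leaves to the full protocol or analysis plan, neither of which is shown.

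Most of this stands, and it limits what can be said. A reader might infer that the trial's true type I error is 8.8%. The documents do not support that: the figure belongs to one reading, near the top of a range that starts at 5%. The 39% and the 23.5 points likewise matter only if a claim or a stop at 100 infants is possible.

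A reader might also infer from the Data processing and monitoring section, where the Chief Investigators and the trial statistician appear and "they will review the results generated for logic", that investigators will see by-arm interim results. That section is about data quality, such as range checks, queries and outliers, and does not describe an interim efficacy review. The Blinding section moreover says that end-point assessors are blinded and that clinicians other than the investigators decide on MV. Neither section adds to this point.

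The condensed format does not remove the concern. The article is not merely silent: it states the interim, the single threshold and the one-look sample size together, and applying them as stated can give the wrong error rate.

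**Conclusion.** The point holds in conditional form. The inflation to about 8.7-8.9% rests on four assumptions: the interim tests the primary endpoint, it uses two-sided P<0.05 (sidedness inferred from the 138 per arm), efficacy can be claimed at either look, and the chi-square test is uncorrected, which is the version that matches the sample size. Changing the last assumption gives about 6%; dropping the third gives 5%.

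What is certain is that the article does not settle which of these applies, and that its 0.05 level is not protected under the only rule it gives. This should be settled before the interim data are examined, because a rule chosen after seeing the result cannot restore the error rate.

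**What to change.** Amend the Statistical analysis section to state one of the following:

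1. The interim is for safety or futility only. No efficacy claim can be made from it, and the final test is at two-sided 0.05.
2. The interim tests the primary endpoint under a pre-stated alpha-spending boundary. One example is Lan-DeMets O'Brien-Fleming-type: two-sided P<0.0011 at 100 infants and P<0.0495 at the final analysis.

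Other valid boundaries exist: Pocock uses 0.0279 at each look, and the O'Brien-Fleming-type function applied at 0.025 per side gives about 0.0004 and 0.0499. The choice matters less than stating it in advance.

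Either way, tie the interim to the 100th infant having completed 72 hours instead of to enrolment, so that the primary endpoint is known for all 100. State that tests are two-sided and whether the chi-square is continuity-corrected.

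The cost is one or two sentences by amendment. Option 1 leaves the final level unchanged. The example boundary in option 2 moves it from 0.05 to 0.0495. No extra infants are needed, and power stays at about 80%.

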### Duration of study

In this study, 272 infants will be recruited. The trial will terminate when the last recruited infant is discharged from hospital, or dies.

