**Methods/Design:**

In this study, 276 infants born at 25^+0^ to 28^+6^ weeks’ gestation at high risk of respiratory distress syndrome (RDS) will be randomized to receive the SLI maneuver (25 cmH_2_O for 15 seconds) followed by nasal continuous positive airway pressure (NCPAP) or NCPAP alone in the delivery room. SLI and NCPAP will be delivered using a neonatal mask and a T-piece ventilator.

The primary endpoint is the need for MV in the first 72 hours of life. The secondary endpoints include the need and duration of respiratory support (NCPAP, MV and surfactant), and the occurrence of bronchopulmonary dysplasia (BPD).

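### Duration of study gives a recruitment total of 272, while the abstract gives 276 and the Sample size section needs 138 per group (276): a minor inconsistency to reconcile

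*Protocol article*

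**What the plan says.** The article states the size of the trial in three places.

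- **Abstract, Methods/Design:** "In this study, 276 infants born at" the eligible gestational ages will be randomized. The total is 276.
- **Sample size:** "138 newborns must be enrolled in each group to detect this difference", "with 80% power at a level of 0.05". The difference is a fall in the need for mechanical ventilation in the first 72 hours from 35% to 20%. The Randomization section says that infants are "randomly assigned to a treatment group in 1:1 ratio", so 138 per group is 276 in total.
- **Duration of study:** "In this study, 272 infants will be recruited". The next sentence ends the trial when the last recruited infant has been discharged or has died.

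The figure 276 is printed once, in the abstract. The Sample size section gives only the number per group. No section states a dropout allowance or separates infants randomized from infants analysed.

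**The concern.** All three statements describe the same quantity, the number of infants to be enrolled, and they cannot all be right. A dropout allowance could not explain the gap, because it would put the number recruited above the calculated 276, not below it. This is not detail that an article leaves to a fuller document: the article prints two incompatible totals.

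At stake is the correctness of a figure the trial relies on. The Sample size section presents 138 per group as a requirement, and the section that describes the end of the trial gives a total that falls short of it. A reader who compares the final enrolment with the plan would not know which figure to use.

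**Working it through.** **Inputs**

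- From the Sample size section: control rate p1 = 0.35, SLI rate p2 = 0.20, difference 0.15, power 80%, level 0.05.
- From the Randomization section: 1:1 allocation.
- Assumed: a two-sided test, since the section does not state sidedness. The one-sided versions of the formula below give 109 per group, or 122 with continuity correction, and neither matches 138.
- Normal quantiles: 1.96 (two-sided 0.05) and 0.8416 (80% power).

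**Step 1: reproduce the plan's own figure.** The pooled-variance formula without continuity correction uses the mean rate (0.35 + 0.20)/2 = 0.275:

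n = [1.96 × √(2 × 0.275 × 0.725) + 0.8416 × √(0.35 × 0.65 + 0.20 × 0.80)]² / 0.15²

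= [1.96 × 0.6315 + 0.8416 × 0.6225]² / 0.0225

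= [1.2377 + 0.5239]² / 0.0225 = 3.1031 / 0.0225 = 137.9

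Rounded up, this is 138 per group and 276 in total. It matches the Sample size section and the abstract.

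**Step 2: see whether another usual formula gives 272.** All are two-sided.

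| Formula | n per group | Rounded up | Total |
|---|---|---|---|
| Pooled variance, no continuity correction | 137.9 | 138 | 276 |
| Pooled variance, continuity correction | – | 151 | 302 |
| Arcsine | 136.75 | 137 | 274 |
| Unpooled variance | 135.2 | 136 | 272 |

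The unpooled formula is (1.96 + 0.8416)² × (0.2275 + 0.16) / 0.0225 = 7.849 × 0.3875 / 0.0225 = 135.2. So 272 could be left over from a different calculation, or it could be a typing error. The article does not say which.

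**Step 3: power at each total.** Inverting the pooled formula, power = Φ[(0.15 × √n − 1.2377) / 0.6225]:

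- n = 138: (1.7621 − 1.2377) / 0.6225 = 0.842, power 80.0%
- n = 136: (1.7493 − 1.2377) / 0.6225 = 0.822, power 79.4%

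The Statistical analysis section names the chi-square test. Its power without continuity correction, found by summing binomial probabilities over all outcomes that the test rejects, is:

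- n = 138: 80.3%
- n = 136: 80.0%

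By the unpooled formula, power at 136 per group is Φ(0.15 × √136 / 0.6225 − 1.96) = Φ(0.850) = 80.2%.

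**Step 4: size of the gap.** 276 − 272 = 4 infants, two per group, or 4/276 = 1.4% of the target. The largest loss of power among these methods is 80.0 − 79.4 = 0.6 points.

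**The case against.** The strongest reply is that nothing of substance turns on four infants. The section that derives the number agrees with the abstract. Duration of study is about when the trial ends and repeats the total in passing, so most readers would take 272 for a slip. The Sample size section names no formula, and 272 still reaches 80% by the exact calculation (80.0%) and by the unpooled formula (80.2%). All of this stands. It limits the importance of the point but does not remove the contradiction.

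A reader might infer three stronger things, and the document supports none of them.

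- **That two totals give the sponsor room to choose when to close an unblinded trial.** The window is four infants, the derivation and the abstract agree, and nothing in the article shows that such a window could steer the result.
- **That the interim analysis is affected.** The fraction would be 100/276 = 36.2% or 100/272 = 36.8%. However, the Statistical analysis section triggers the look by a count of 100 infants and states no boundary that uses a fraction. The look falls at the same infant under either total.
- **That the trial would be underpowered at 272.** The shortfall appears only under the pooled formula, and there it is about 0.6 points. That this was the formula used is inferred from its match with 138; it is not stated.

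**Conclusion.** The total of 272 in Duration of study is wrong as written, because it conflicts with the abstract and with the number per group in the Sample size section. The stated inputs reproduce 138 per group, so 276 is the total that the article supports. This rests on a two-sided test and the pooled formula without continuity correction, neither of which the article states; among the variants tried, that combination is the one that gives 138.

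The point is minor. The gap is four infants and the effect on power runs from about 0.3 points (exact) to about 0.6 points (pooled formula). No test, error rate, comparison or safety provision changes.

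**What to change.** Change 272 to 276 in Duration of study, so that it agrees with the abstract and the Sample size section.

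If 272 is the intended total, restate the abstract as 272 and the Sample size section as 136 per group, and name the formula together with the power it gives. The power should not simply be entered as 79.4%, because the value depends on the method: 79.4% pooled, 80.0% exact, 80.2% unpooled.

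The first option costs one number. The Trial status section says that recruitment is still open, so the correction can be made before enrolment closes.

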## Quality control and quality assurance procedures

### Compliance to protocol

Compliance will be defined as full adherence to protocol. Compliance with the protocol will be ensured by a number of procedures as described below.

### Site set-up

Local principal investigators participated in preparatory meetings in which details of the study protocol, data collectionand SLI procedure were accurately discussed. All centers received detailed written instruction on web-based recording data and, to resolve possible difficulties, it will be possible to contact the Clinical Trials Coordinating Center (LB). Moreover, it has been ascertained that the SLI procedure is equally made in all participating centers, to avoid expensive visits for training at each site due to the limited resources available for this study.

### Data processing and monitoring

All study data will be:

1. Screened for out-of-range data, with cross-checks for conflicting data within and between data collection forms by a data manager.

2. Referred back to the relevant center for clarification in the event of missing items or uncertainty.

3. Reviewed by the Chief Investigators (CD, GL) and trial statistician, and they will review the results generated for logic,patterns andproblems Outlier data will be investigated.

### Safety

Safety end-points will include incidence, severity and causality of reported SAEs, namely changes in occurrence of the expected common prematurity complications and clinical laboratory test assessments, and the development of unexpected SAEs in this high risk population. All SAEs will be followed until satisfactory resolution or until the investigator responsible for the care of the participant deems the event to be chronic or the patient to be stable.

All expected and unexpected SAEs, whether or not they are attributable to the study intervention, will be reviewed by the local principal investigators to determine if there is a reasonable suspected causal relationship with the intervention. If the relationship is reasonable, SAEs will be reported to the Chief Investigators who will then report them to the Ethics Committee and inform all other investigators to guarantee the safety of the participants.

## Trial status

The Local Ethics Committee approved the study and the trial is currently recruiting study subjects.

## Abbreviations

AAP: American Academy of Pediatrics; BDP: bronchopulmonary dysplasia; BiPAP: bi-level nasal continuous positive airway pressure; BPD: bronchopulmonary dysplasia; BW: birth weight; FRC: functional residual capacity; GA: gestational age; HFV: high frequency ventilation; IMV: intermittent mandatory ventilation; INSURE: intubation-surfactant-extubation; IVH: intraventricular hemorrhage; MAP: mean airway pressure; MV: mechanical ventilation; NCPAP: nasal continuous positive airway pressure; NEC: necrotizing enterocolitis; NICU: neonatal intensive care unit; NIMV: nasal intermittent mandatory ventilation; PDA: patent ductus arteriosus; PEEP: positive end-expiratory pressure; PIP: peak inspiratory pressure; PSV: pressure support ventilation; PVL: periventricular leukomalacia; RDS: respiratory distress syndrome; ROP: retinopathy of prematurity; RR: relative risk; SAE: serious adverse event; SIMV: synchronized intermittent mechanical ventilation; SIPPV: synchronized intermittent positive pressure ventilation; SLI: sustained lung inflation; VG: volume guarantee; VILI: ventilator-induced lung injury
